##### Individual level

3.6.2.1

This is the level at which individuals are impacted directly, including older community members, volunteers and health and social service providers.

For older community members, we will consider the primary outcome as a mean change in loneliness, from baseline at 3, 6 and 12 months for participants receiving the *Connect Local* program, when compared to the comparator group. This will be measured using UCLA-3 as informed by previous research that support the sample size calculations (58). At this stage, there is insufficient research data to calculate sample size when using UCLA-4 (57), however this tool has been recommended for use by community organisations by Australia’s national network, Ending Loneliness Together (71), therefore we will also utilise this tool to capture loneliness to ascertain whether it can be utilised with this cohort in future studies.

As outlined in Tables 2, 3, secondary outcomes, including social isolation, social anxiety, depressive symptoms, and improvement in quality of life and wellbeing, are a mean change from baseline at 3, 6 and 12 months for participants receiving the *Connect Local* program, when compared to the comparator. Achieved goals, as measured by the Goal Attainment scale (64), will also be gathered from the intervention group.

For community volunteers involved in the *Connect Local* program, as per Tables 2, 3, we will collect health-related quality of life and wellbeing measures at baseline, 3, 6 and 12 months.

Perceptions of the program will be collected from community members in the intervention group, volunteers and service providers involved in referred to the *Connect Local* program through interviews or focus groups at three months from participant baseline. Questions will invite participants to share their thoughts around the following aspects of the program: Relational (trust and trustworthiness, obligations and expectations, identity and identification), Cognitive (shared language, codes and narratives; shared values, attitudes and beliefs; and shared goals and purpose), and Structural (roles, rules, precedents and procedures).

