###### Sample size calculation

3.6.2.3.1

The primary outcome is a reduction in loneliness at 3 months for participants receiving the *Connect Local* program, when compared to the comparator group. A program conducting similar activities found a statistically significant reduction in mean UCLA-3 scores of 0.85, with a medium effect size of 0.37 (73). Using this effect size at 0.05 alpha, 76 participants are required in the intervention group to reach 0.9 power. Allowing for 15% attrition at the 3 month follow up, we have increased the sample size to 88. A matched comparator group will be recruited at a 1:1 ratio, as such a total of 176 participants will be recruited to the intervention and comparator groups.

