##### Quantitative data analysis

3.7.1.1

For all quantitative, repeated, continuous individual level variables (loneliness, social isolation, social anxiety, depressive symptoms, wellbeing, quality of life) the main research question will be whether the study intervention is effective at improving the outcome of interest compared with usual care. Modelling these data will focus on fitting linear mixed models using different covariance matrices such as: unstructured, an exchangeable-changeable and AR level-1 residual matrices, where the mean structure of all fitted models include a term for intervention group and a term for time and an interaction term for time and intervention. Non-linear outcomes will be fitted using Generalised Estimating Equations (GEE) analysis which requires that the missingness mechanism is Missing Completely At Random (MCAR). Alternatively, polynomials and/or piecewise linear functions will be utilised for modelling outcomes with non-linear growth trajectories if responses are Missing At Random (MAR). To ascertain whether the missing data is MCAR or MAR, we will utilise methods such as data inspection, applying domain knowledge and comparing summary statistics between cases with complete data and those with missing data to determine the missing data mechanism. An understanding of the mechanism will enable an appropriate statistical method to be chosen to handle the missing values in the data set.

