For quantitative, binary or dichotomous individual level outcomes (scales that have cut-off scores: loneliness (UCLA-3), social anxiety, depressive symptoms) additional analysis will be undertaken addressing the research question: do the interventions differ in their effectiveness, such that individuals in the intervention group experience a greater improvement in their probability of achieving the desired outcome compared to those receiving usual care. Generalised linear mixed models (GLMMs) for dichotomous outcomes will be used as well as GEE. The typology of missing data will be investigated to make sure that the assumptions of the adopted statistical technique are not violated. Our choice of GLMMs is based on the specific characteristics of the data, as well as the advantages provided by GLMMs in handling dependent responses in longitudinal or repeated measures studies. As highlighted in Breslow and Clayton (75), GLMMs incorporate random effects into the linear predictors and are particularly well-suited for modelling the dependence among response variables in such study designs.

Selection of the model that best fits the data will be based on the low goodness-of-fit measures such as the Akaike information criterion (AIC) and Bayesian information criterion (BIC). Additionally, the log-likelihood ratio test will be employed as another method for evaluating model fit.

All quantitative community and system level variables, as well as the goal attainment will be analysed descriptively. Descriptive statistics will be presented as proportions, means (standard deviations) or, for variables that did not conform to a normal or log-normal distribution, medians (interquartile range).

Statistical analysis will be performed using STATA V.15.0 (STATA Corp LP., College Station, Texas, United States). We will use a Type I error rate of 5% to indicate statistical significance, with 95% confidence intervals (CI).

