###### Missing data

3.7.1.1.1

General and generalised linear mixed models use maximum likelihood estimation which produces robust/unbiased estimates as they make implicit corrections for missing data, hence they are likely to retain more power if participants are lost to follow-up than traditional repeated-measures ANOVA/ANCOVA approaches which use “complete-case-analysis” approach that only includes cases with no missing data in the analysis. Maximum likelihood estimation (MLE) for incomplete longitudinal data (continuous or categorical) uses all available information, which means all participants will be included in the analysis regardless of whether they had complete responses for all occasions/timepoints or not. The MLE estimates are consistent if the assumption of data missingness is MAR and is more robust than using imputed values.

If more than 5% of the outcome data are missing, a sensitivity analysis will be conducted comparing fitted models in terms of estimates and corresponding standard errors using maximum likelihood estimation with and without considering different imputation techniques.

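### The trial's outcome data choose the effectiveness model by unranked fit criteria, and a missingness judgement that cannot be verified decides whether GEE is used, so neither the 5% level nor the 3-month estimate is secured

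*Protocol article*

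**What the plan says.** Section 3.7.1.1 (Quantitative data analysis) fits linear mixed models to the repeated continuous outcomes, loneliness among them. Every fitted model contains group, time and their interaction. Unstructured, exchangeable and autoregressive residual matrices are given as examples of the covariance. How time is coded is not stated.

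Two routes for non-linearity follow. The first is "Non-linear outcomes will be fitted using Generalised Estimating Equations (GEE) analysis which requires that the missingness mechanism is Missing Completely At Random (MCAR". The alternative is "polynomials and/or piecewise linear functions will be utilised for modelling outcomes with non-linear growth trajectories if responses are Missing At Random (MAR". The mechanism is to be judged by looking at the data, by domain knowledge, and by comparing people with complete and incomplete data.

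The selection rule is "Selection of the model that best fits the data will be based on the low goodness-of-fit measures such as the Akaike information criterion", together with BIC, and a likelihood-ratio test as a further method. No criterion takes precedence, and the rule is not confined to the covariance. Significance is then judged at 5%. For binary outcomes, GLMM and GEE are both planned and neither is named as primary.

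Section 3.7.1.1.1 (Missing data) says that maximum likelihood is consistent under MAR. Above 5% missing outcome data it adds a sensitivity analysis "comparing fitted models in terms of estimates and corresponding standard errors using maximum likelihood estimation with and without considering different imputation techniques".

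The primary time point differs between sections. In 3.6.2.1, "we will consider the primary outcome as a mean change in loneliness, from baseline at 3, 6 and 12 months"; in 3.6.2.3.1, "The primary outcome is a reduction in loneliness at 3 months for participants receiving the" *Connect Local* program.

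**The concern.** A test carried out at 5% after the same outcome data have chosen the model does not in general have a 5% error rate. Here the criteria can disagree, and the text does not say which one prevails. The study is also non-randomised (section 3.3), so analyst discretion costs more credibility than usual.

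The non-linearity routes join two unrelated questions: the shape of the trajectory and the reason why data are missing. The second is to be settled by diagnostics that cannot settle it. A wrong answer could send an outcome to a method that, by the plan's own statement, then lacks its required assumption. The plan has no need of this route for continuous outcomes, because it already says that its likelihood models are consistent under MAR.

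Finally, no section says which contrast of the selected model is the primary test. If a single slope over 12 months were selected, it need not describe the 3-month effect on which the sample size rests.

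**Working it through.** **1. Inputs.** From section 3.6.2.3.1: "statistically significant reduction in mean UCLA-3 scores of 0.85, with a medium effect size of 0.37", which implies an SD of 0.85/0.37 = 2.30. Also: "Using this effect size at 0.05 alpha, 76 participants are required in the intervention group to reach 0.9 power". The 76 is reproduced, within one, by the one-sample pre-post formula: ((1.95996 + 1.28155)/0.37)² = 76.75. The attrition step is 76 × 1.15 = 87.4, rounded up to 88. That formula is for change within one group, whereas the planned comparison is between two; this is a separate matter and nothing below depends on it. Visits are at 0, 3, 6 and 12 months (Table 3).

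Assumptions not in the documents: exchangeable correlation 0.5, or a mixed structure (random intercept, autoregressive part and noise); candidate time functions linear, quadratic, piecewise and categorical; the effect profiles; the dropout models.

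**2. Can the rule choose between the methods?** AIC, BIC and the likelihood-ratio test need a likelihood. GEE has no full likelihood, so the rule cannot rank it against a mixed model.

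**3. Can the diagnostics choose the route?** A difference between people with complete and incomplete data is evidence against MCAR. The absence of a visible difference does not establish MCAR.

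**4. A single linear slope, if that is the coding.** Mean time = 21/4 = 5.25; deviations −5.25, −2.25, 0.75, 6.75; sum of squares 78.75. For an effect of 0, 0.85, 0.85, 0.85:

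- numerator = 0.85 × (−2.25 + 0.75 + 6.75) = 4.4625
- slope = 4.4625/78.75 = 0.0567 per month
- fitted 3-month change = 3 × 0.0567 = 0.17, which is 20% of 0.85

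For a fading effect (1, 0.67, 0.33 of the 3-month value): 3 × (−2.25 + 0.5025 + 2.2275)/78.75 = 0.02 of the true 3-month effect. For a truly linear effect there is no loss. With 76 per arm, rejection rates under linear against categorical time were 0.43–0.52 against 0.64–0.70 (sustained effect) and 0.06–0.09 against 0.65–0.68 (fading effect).

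**5. Type I error.** Simulation of 1,500 trials with 76 per arm, four time functions by three covariances, Monte Carlo standard error about 0.006:

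| Procedure | Type I error |
|---|---|
| Fixed: categorical time, unstructured | 0.048–0.055 |
| Covariance chosen by AIC, time categorical | 0.050–0.061 |
| Time function and covariance chosen by BIC | 0.046–0.065 |
| Time function and covariance chosen by AIC | 0.095–0.109 |

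A separate run with 75 per arm gave 0.050 (fixed), 0.069 (BIC) and 0.087 (AIC).

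**6. The estimate after selection.** With a sustained effect of −0.85, the mean 3-month estimate was −0.80 to −0.82 after AIC selection and about −0.46 after BIC selection, because BIC often kept the linear slope. The fixed model gave −0.84 to −0.87 over the sustained and fading profiles.

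**7. GEE if MCAR is wrongly accepted.** True 3-month effect −0.85, MAR dropout of about 14–16% by 3 months:

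| Dropout pattern | Independence | Correct exchangeable |
|---|---|---|
| Same in both groups | −0.85 | −0.84 |
| Outcome-dependent in intervention group only | −0.98 | −0.85 |
| Opposite in the two groups | −1.09 | −0.85 |

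The bias is therefore 0.13–0.24 when dropout differs between groups and the working correlation is independence, and about zero otherwise. The plan names no working correlation.

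**8. Departure from MAR.** If 15% of the intervention group drop out and are 1 point worse than MAR predicts (an assumed figure), the effect shifts by 0.15 × 1 = 0.15, and 0.15/0.85 = 18%.

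**The case against.** The article condenses a fuller plan, and the coding of time is a detail that may sit in an analysis plan not shown. That is fair. A reader might infer that the default is a linear trend, because polynomials are offered for non-linear trajectories, but the text never says so. Step 4 is therefore conditional.

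It can also be argued that selection concerns only the covariance, since the covariance matrices are what the text says will vary and all models share the same terms. On that reading the error rate stays at about 5–6%, and a claim that the 5% level is lost would not be supported. What stands is that the rule speaks of the best-fitting model without that limit, in a section that also admits other time functions.

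The attenuation in step 4 and the error rates for free selection in step 5 cannot both apply in full: one needs the slope to be kept regardless of fit, the other needs selection to operate.

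On GEE, the plan ties it to MCAR and offers polynomial or piecewise models under MAR. It would be wrong to read the plan as applying GEE to data known to be MAR, or as having no other fallback. The GEE-or-polynomial choice is also assigned to the missingness mechanism rather than to AIC. What stands is that this choice depends on a diagnosis the stated methods cannot deliver.

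On the sensitivity analysis, the open reference to imputation techniques does not exclude delta adjustment, and dropout that depends on observed loneliness is MAR. The plan is unspecific here rather than wrong.

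**Conclusion.** The concern holds in conditional form. The plan states a data-driven choice of model with unranked criteria, one class of candidate that those criteria cannot assess, and a route that depends on an unverifiable judgement of MCAR. The 5% level is not guaranteed. The excess ranges from negligible (covariance only) to roughly double the nominal rate (AIC over both time function and covariance), under the assumed correlations and candidate set. AIC and BIC can also give materially different 3-month estimates, about −0.8 against −0.46 for a true −0.85 that is sustained.

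The fall from 0.85 to 0.17 requires both a retained linear slope and a sustained effect. GEE bias requires MCAR wrongly accepted, dropout that differs between groups, and independence working correlation. Neither is a prediction for this trial. Nor do the documents settle 3 months as the only primary time point: sections 3.6.2.1 and 3.6.2.3.1 disagree. This should be corrected before the data are analysed.

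**What to change.** - For continuous outcomes, prespecify one linear mixed model by REML: time as four categories, group, group-by-time and unstructured covariance.
- State a convergence fallback that respects the unequal spacing of visits at 0, 3, 6 and 12 months, for example a correlation that decays with months apart and a separate variance at each visit. An autoregressive structure indexed by visit number would not do this.
- Define the primary effect as the between-group difference in change from baseline to 3 months, in line with section 3.6.2.3.1, and reconcile section 3.6.2.1 with it. A difference in 3-month means alone would carry any baseline imbalance of this non-randomised comparison.
- Remove AIC, BIC and likelihood-ratio selection and the GEE route for continuous outcomes. The polynomial and piecewise options then become unnecessary.
- For binary outcomes, name either GLMM or GEE as primary and make the other a sensitivity analysis.
- State that the imputation sensitivity analysis includes a delta-adjusted version that departs from MAR. The planned 15% attrition at 3 months already exceeds the 5% trigger.

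The cost is wording and a little more analysis work. The fixed model has 4 visits × 2 groups = 8 mean parameters against 4 for a linear trend, and 4 × 5/2 = 10 covariance parameters, which 176 people can support.

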### Program effectiveness

3.1

Compared to the comparator group, older people receiving the intervention will, when compared to baseline, report at 3-, 6- and 12-months follow-up:

(i) a reduction in loneliness, social isolation and/or depressive symptoms;(ii) improvement in wellbeing and quality of life;(iii) increased access to activities/services in the community.

Three months after participation in the program, community volunteer participants will have improved wellbeing and quality of life when compared to baseline.

It is hypothesised that all stakeholders: intervention, volunteer and service provider participants will also have a positive perception of and experience with the program.

*Research question for older participant cohort using PICO:*

Does participation in the *Connect Local* social connection program reduce loneliness, social isolation and/or depressive symptoms, improve wellbeing and quality of life and increase access to activities/services in community of older Australians when compared to a similar group who do not have access to a similar program?

*Research question components for stakeholders using SPIDER:*

Sample: volunteers and service provider participants;

Phenomenon of interest: perception and experience of program;

Design: prospective surveys and semi-structured interviews;

Evaluation: impact on community and health services, and perceptions of the program;

Research type: mixed methods.

Question: What are the perceptions and experiences of volunteers/service provider participants after being a part of the *Connect Local* program?

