#### Older community members: intervention group

3.5.1

The inclusion criteria include being aged 65 years or older; understand and speak English sufficiently to understand and be involved in the program; live in the target LGA; community dwelling (including those experiencing homelessness); have at least one chronic health condition; are at risk or experiencing loneliness, social isolation and/or depressive symptoms. Screening tools are summarised in Table 2, loneliness will be assessed using both the Single Item Measure and UCLA-3 as per recommended national indicators of loneliness (66).

**Table 2 tab2:** Intervention outcome evaluation methods.

Evaluation component *Definition*	Indicators	Methods and tools
Individual level *Impacting individuals directly*	*Older person participants:*	
	Loneliness	Single-item measure of loneliness: How often do you feel lonely?, responses: often or always, some of the time, occasionally, hardly ever or never (often or always, some of the time indicating loneliness)	UCLA-4 (57)
UCLA-3 (score of ≥6 indicates at risk of loneliness) (58)
Social isolation	Lubben-6 (score ≤ 12 indicates at risk for social isolation) and − 18 (59);
Social anxiety	Mini-SPIN (Social Phobia Inventory, SPIN) (60);
Depressive symptoms	GDS-5 (score of ≥2 is indicative of depression) (61);
Wellbeing and quality of life	Physical wellbeing (and QoL): EQ-5D-5L (62); Mental wellbeing: Warwick-Edinburgh Mental Wellbeing Scale (WEMWBS) (63);
Goals attained^+^	Goal Attainment (64)^+^.
Perceptions of program^+^	Interviews on perceptions of the program^+^.
*Service providers:*	
Perceptions of program	Interviews/focus groups on perceptions of the program.
*Volunteers:*	
Wellbeing and quality of life	Physical wellbeing (and QoL): EQ-5D-5L (62); Mental wellbeing: Warwick-Edinburgh Mental Wellbeing Scale (WEMWBS) (63);
Perceptions of program	Interviews/focus groups onperceptions of the program.
Community level *Impacting broader community*	*Older person participants:*	
	Access to activities/services Number and types of services offered to participants	Resource use questionnaire [adapted from Fletcher et al. (65)]
	*Community service providers:*	
	Impact of program on community services	Community service impact survey [adapted from NHS (56)]
	Community service provider Satisfaction with program	Interview/focus group with community service providers

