Health system level *Impacting at the health service level, including hospitalisations, GP visits and other health service visits.*	*Older person participants:*	
	ED presentations; Hospitalisations; Hospital length of stay Number of GP consultations Number of GP care plan reviews	Resource use questionnaire [adapted from Fletcher et al. (65)]
	*Health Service providers:*	
	Perspectives of staff in general practice and other referral agencies Health provider satisfaction	Interviews/focus groups

^+^Data not being collected from community members in comparator group.

The exclusion criteria include living in residential aged care; individuals who do not speak English sufficiently to understand the program; and individuals who do not have the cognitive capacity to consent [assessed using a Cognitive Capacity to Consent Checklist (67)].

All eligible individuals will be made aware of the evaluation by the Community Connector and asked if their details can be shared with the researchers to contact them about the study. The researchers will contact the individuals to obtain consent. If consent is obtained, individuals will be asked if they would like to be informed of trial results.

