##### Community level

3.6.2.2

As per Table 2 the following indicators will be collected to evaluate the impact of the program on the broader community: the number of participants who access community activities/services, the number and types of services offered to and used by participants in both the intervention and comparator groups at baseline, 3, 6 and 12 months using the Resource Use Questionnaire [adapted from Fletcher (65)].

We will also ask community service and/or activity providers about the impact of the program on their services six monthly, using the Community Service Impact Survey (72), and their perspectives of the program through interviews or focus groups at three months from when participants were engaged in their program.

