##### System level

3.6.2.3

To evaluate impact of *Connect Local* on health services use such as hospitalisations, General Practitioner (GP) visits and other health service visits, several health service-related indicators will be collected from participants in both the intervention and comparator groups at baseline, 3, 6 and 12 months using the Resource Use Questionnaire [adapted from Fletcher (65)], as per Tables 2, 3. Using interviews, the service provider morale in general practice and other referral agencies and healthcare provider satisfaction will also be gathered at three months from when their patients engaged in the *Connect Local* program.

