##### Evidencing outcomes and giving them a value

3.6.3.1

Data on loneliness, social connection, depressive symptoms, wellbeing, quality of life and health service use at baseline, 3, 6 and 12 months will provide evidence of outcomes, drawing comparisons between the intervention and comparator groups. Each outcome will be then monetised using financial proxies. Costs and benefits that occur at different time points will be made comparable by adjusting for inflation in order to calculate net present value (47).

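### Hypothesis 3.1(iii), more access to activities and services than the comparator, is given only a descriptive analysis, so the plan produces no between-group estimate, interval or test for it

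*Protocol article*

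**What the plan says.** The hypotheses for older participants in Section 3.1 (Program effectiveness) open with: "Compared to the comparator group, older people receiving the intervention will, when compared to baseline, report at 3-, 6- and 12-months follow-up". Three items follow: (i) loneliness, social isolation and/or depressive symptoms; (ii) wellbeing and quality of life; and (iii) "increased access to activities/services in the community". The PICO question in the same section repeats the access item and again sets it against a similar group without the program.

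Table 2 lists "Access to activities/services Number and types of services offered to participants" under the community level, measured by the Resource Use Questionnaire. Section 3.6.2.2 (Community level) says that, at all four time points, the data will cover how many participants access activities or services, and "the number and types of services offered to and used by participants in both the intervention and comparator groups".

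Section 3.7.1.1 (Quantitative data analysis) specifies linear mixed models with group, time and group-by-time terms for continuous individual-level outcomes, and GLMM and GEE for dichotomised individual-level scales. For everything at the other two levels it says: "All quantitative community and system level variables, as well as the goal attainment will be analysed descriptively". The formats named are proportions, means with SD, and medians with IQR.

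**The concern.** A hypothesis about change relative to a comparator needs an estimate of that difference and a statement of its uncertainty. The analysis section supplies both for (i) and (ii) and, by the way Table 2 classifies access, withholds both for (iii).

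Access matters more than most secondary outcomes here. The Community Connector's task is to link people to local activities and services, so uptake is the first step by which the program could reduce loneliness. If loneliness does not change, the authors will want to know whether access changed. If loneliness does change, they will want to show that access moved with it.

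The design also makes unmodelled summaries hard to read. The study is non-randomised. Matching is on age and gender only. Comparators come from the tertiary hospital and the aged and community care provider, while intervention participants also arrive through general practice, the website and general community access. Baseline use of services may therefore differ, and separate summaries at each visit do not give the difference in change from baseline that the hypothesis describes.

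**Working it through.** **Step 1. What each comparative hypothesis receives.**

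| Hypothesis in 3.1 | Level in Table 2 | Data in both groups, four visits | Analysis in 3.7.1.1 |
|---|---|---|---|
| (i) loneliness, isolation, depressive symptoms | Individual | Yes | Mixed model with group, time, group-by-time; GLMM/GEE for UCLA-3 and depressive symptoms dichotomised at a cut-off |
| (ii) wellbeing, quality of life | Individual | Yes | Mixed model with group, time, group-by-time |
| (iii) access to activities/services | Community | Yes (3.6.2.2) | Descriptive |

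The variables listed for the mixed models, and the scales listed for GLMM and GEE, do not include access. The gap in (iii) follows from its level in Table 2, not from missing data.

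**Step 2. Can the gap be left to an analysis plan?** No. The sentence covers all quantitative variables at the community and system levels and fixes the method. An analysis plan that modelled access would contradict it.

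**Step 3. What the sample can show for access.** The protocol gives no rate, SD or power for access. Its only sample-size figure is for UCLA-3: effect size 0.37, alpha 0.05, power 0.90, 76 in the intervention group. That figure reproduces as a one-group calculation:

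- n = ((1.960 + 1.282) / 0.37)² = 76.75, against the stated 76.

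Taking 76 per group at a single visit, two-sided 5%:

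- Detectable standardised difference = (1.960 + z_power) × √(2/76), with √(2/76) = 0.1622.
- 80% power: (1.960 + 0.842) × 0.1622 = 0.45 SD.
- 90% power: (1.960 + 1.282) × 0.1622 = 0.53 SD.

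For any use (yes/no), with an **assumed** comparator proportion of 30% to 60%:

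- Power = Φ((Δ − 1.960 × SE₀) / SE₁), where SE₀ = √(2p̄(1 − p̄)/76) and SE₁ = √((p₁(1 − p₁) + p₂(1 − p₂))/76).

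| Assumed difference | Power across comparator 30–60% |
|---|---|
| +10 points | 23–25% |
| +15 points | 46–51% |
| +20 points | 70–77% |
| +25 points | 88–94% |

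Interval width at an assumed 30% versus 50%: SE₁ = √((0.21 + 0.25)/76) = 0.0778, so the 95% CI is ±1.960 × 0.0778 = ±0.152, about ±15 points.

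These are single-visit approximations. They ignore any gain from the baseline measurement and any loss after 3 months.

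**The case against.** **Describing secondary outcomes is defensible.** In a pragmatic convenience sample sized for UCLA-3 alone, a descriptive report of service variables is a reasonable choice, and formal tests would often be underpowered. This stands for variables with no hypothesis attached. It does not settle (iii), where the protocol has committed to a comparison. Low power is a reason to show the interval, or to soften the hypothesis.

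**The hypothesis is not wholly out of reach.** A reader might infer that (iii) can be neither supported nor refuted. That is too strong. Proportions and counts by group and visit would bear on it. What is missing is an estimate of the differential change and its uncertainty.

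**The general 5% error rate and 95% CIs.** Section 3.7.1.1 states these for the analysis as a whole. They do not fill the gap, because the descriptive formats provide no between-group quantity for an interval to attach to.

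**Health-service use and the SROI.** Table 2 puts "ED presentations; Hospitalisations; Hospital length of stay Number of GP consultations Number of GP care plan reviews" at health system level, so the same sentence covers them. A reader might infer that the SROI therefore has no between-group estimate, or rests on medians that cannot yield a mean cost. The document does not support this. The descriptive sentence belongs to Outcome 1, and the economic evaluation is Outcome 2 with its own method. Section 3.6.3.1 says that data on "wellbeing, quality of life and health service use at baseline, 3, 6 and 12 months will provide evidence of outcomes", with comparisons between the two groups. Box 1 derives deadweight from comparator data, uses comparator information for displacement, and deducts both. Nothing says that the Section 3.7.1.1 medians feed the ratio. Nor is health-service use one of the hypotheses in 3.1; it enters through the return-ratio hypothesis in 3.2. It is also not safe to infer that medians alone would hide a difference, since the planned summaries include IQRs and proportions.

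**Conclusion.** The contradiction is real and confined to 3.1(iii). One of the three comparative hypotheses for older participants has data in both groups at all four time points, yet the analysis section assigns it summaries only. It is worth correcting before analysis. It does not affect the primary outcome, hypotheses (i) and (ii), or the structure of the SROI.

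The finding rests on Table 2's placing of access at community level and on the word "all" in the analysis sentence; it does not depend on any assumed figure. The power and interval figures do rest on assumed access rates and on 76 per group. They show only what precision to expect: a difference of 20 points or more might be detected reasonably well, and one of 10 points would not.

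**What to change.** In Section 3.7.1.1, take access to activities/services out of the descriptive-only sentence and analyse it with the group, time and group-by-time terms already specified for the individual-level outcomes:

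- **Any use:** logistic mixed model, which is within the GLMM class the section already names.
- **Number of activities or services used:** negative binomial mixed model.
- **Reporting:** between-group effects at 3, 6 and 12 months with 95% CIs, with time entered by visit so that each interaction term is the change from baseline relative to the comparator.

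If the authors prefer to keep access descriptive, reword 3.1(iii) and the matching part of the PICO question as a descriptive aim. Either change removes the contradiction.

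Health-service use is optional. Section 3.6.2.3 (System level) sets out to evaluate impact on it, and the data are "collected from participants in both the intervention and comparator groups at baseline, 3, 6 and 12 months using the Resource Use Questionnaire". Between-group differences in means with 95% CIs could sit beside the descriptive summaries at little cost. Goal attainment should stay descriptive, as it is not collected in the comparator group.

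The cost is a few extra models and no new data. Intervals will be wide because the sample was sized for UCLA-3 only. The models will not remove confounding from the non-randomised design, so the estimates should be presented with that caution.
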